### Primary outcome

2.7

The primary outcome variable is any change in the total EPDS score (31) from baseline at 13–18 weeks of gestation to 11 weeks after randomization. The EPDS is a standard 10-item self-report questionnaire, which was originally developed to screen for postpartum depression. It has been widely validated to detect depression both during (Cronbach’s α = 0.82–0.84) (32) and after pregnancy (Cronbach’s α = 0.87) (31). However, it has not been validated specifically in Finland. The respondents are asked about symptoms of depression in the past week. The score ranges from 0 to 30, and 13 points or above is normally used as a cutoff for depression during pregnancy. Because this study focuses on early intervention, we use a cutoff of 10 points on the total EPDS score to ensure that we include pregnant women with subclinical depressive symptoms (18, 33). The primary and secondary outcomes have been described in detail in **Table 3**.

**Table 3 T3:** The schedule of enrollment, interventions, and assessments.

	Enrollment		Allocation	Post-allocation		
Time point		T0		Intervention period	T1	T2
Enrollment						
EPDS screen	X					
Informed consent	X					
Eligibility screen	X					
MINI interview	X					
Allocation			X			
Intervention						
iCBT intervention group				iCBT with telephone coaching		
Educational control group				Online psychoeducation		
Assessments						
*Depression*						
Symptoms of antenatal depression (primary outcome) EPDS		X				X
Depressive symptoms BDI-II		X				X
*Anxiety*						
Generalized anxiety GAD-7		X				X
Pregnancy-related anxiety PRAQ-R2		X				X
Social phobia SPIN		X				X
*Other measures*						
Maternal attachment MAAS		X				X
Perceived stress PSS		X				
Quality of life and sleep		X				X
*Treatment-related measures*						
Alliance WAI-SR					X	
Use of the digital content					X	
Satisfaction CSQ-I					X	
Biological samples						
Serum sample		X				
Buccal cell swab		X				X

T0 is baseline, T1 is immediately after the intervention, and T2 is 11 weeks after randomization.

EPDS, Edinburgh Postnatal Depression Scale; BDI-II, Beck Depression Inventory-II; GAD-7, Generalized Anxiety Disorder 7-Item Scale; MINI, Mini-International Neuropsychiatric Interview; PRAQ-R2, Pregnancy-Related Anxiety Questionnaire-Revised; SPIN, Social Phobia Inventory; MAAS, Maternal Antenatal Attachment Scale; PSS, Perceived Stress Scale; WAI-SR, The Working Alliance Inventory-Short Revised; CSQ-I, Client Satisfaction Questionnaire; iCBT, internet-assisted cognitive behavioral therapy.

### Secondary outcomes

2.8

*Depression.* The Beck Depression Inventory-II (BDI-II) (34) is also used to examine depressive symptoms. It is a widely used 21-item self-report instrument measuring the severity of depression with high validity and reliability: Cronbach’s α is 0.88 when used during pregnancy and 0.89 among postpartum women (35). In Finland, the scale has been validated for adult populations (36). Each item is scored from 0 to 3, and the total score, which we will evaluate, ranges from 0 to 63. The BDI can be used to assess the nine symptoms of depression included in the Diagnostic and Statistical Manual of Mental Disorders, Fifth Edition (37).

*General anxiety.* The total score of the Generalized Anxiety Disorder 7-Item Scale (GAD-7) is used to assess changes in anxiety symptoms from baseline to follow-up. GAD-7 is a brief screening measure for generalized anxiety (38) with good reliability (Cronbach’s α = 0.89). It includes seven questions about anxiety symptoms in the last 2 weeks, and the frequency is rated from *not at all* to *nearly every day*. A total score of nine indicates potentially clinically significant anxiety symptoms. The GAD-7 has been validated for pregnant women (39) and for use in Finnish primary care settings (40).

*Pregnancy-related anxiety.* Changes in anxiety symptoms related to pregnancy are assessed using the second revision of the Pregnancy-Related Anxiety Questionnaire (PRAQ-R2) (41). This version can be administered to pregnant women regardless of parity. The scale has been implemented and validated in Finland and has shown sufficient reliability (Cronbach’s α = 0.71–0.85 depending on parity and pregnancy week) (41). It consists of 10 items with three subscales: fear of giving birth, worries about delivering a physically or mentally handicapped child, and concerns about the woman’s appearance. We will evaluate the total score and the three subscales separately.

*Social anxiety.* Changes in social anxiety symptoms are assessed using the total score of the Social Phobia Inventory (SPIN), which contains 17 items about avoidance and fear of embarrassment. Each item is rated on a scale of 0 to 4, with higher scores indicating greater distress. A result of 19 points or above on the SPIN is considered indicative of social phobia. The SPIN has demonstrated good test–retest reliability, internal consistency (Cronbach’s α = 0.82–0.94), and validity (42). In Finland, it has been validated for adolescents (43), but not for pregnant women.

*Stress.* The Perceived Stress Scale (PSS) (44) examines changes in personal stress levels. The 10-item scale covers stressful feelings and thoughts during the last month, ranging from 0 for *never* to 4 for *very often*. The total score, which we will evaluate, ranges from 0 to 40, with a higher score indicating greater perceived stress. Cronbach’s α for this instrument is between 0.84 and 0.86, and it has been validated for pregnant women (45). In Finland, it has been validated for measuring stress symptoms of undergraduate students (46).

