Previous randomized controlled trials (RCTs) on iCBT for antenatal depression have reported promising efficacy for reducing core symptoms of depression (21, 23, 24) with high acceptability of the iCBT interventions (21, 23). Attrition rates have been lower in guided than unguided iCBTs (18, 19, 23), and guided programs had higher effect sizes (19). However, studies on iCBT for antenatal depression have relied on small sample sizes and measured outcomes with self-reports only, posing a risk for overall assessment bias (19). No previous evidence exists of the effectiveness of iCBT for symptoms of antenatal depression in pregnant women screened at the population level. Larger population-based studies are needed to replicate previous findings from smaller studies and to identify effective treatment options for pregnant women whose mental health problems impact not only themselves but their offspring as well.

The aim of this study is to examine the efficacy of the *Stronger Together* iCBT intervention for symptoms of antenatal depression in adult pregnant women in Finland. An ideal antenatal iCBT intervention should facilitate and integrate service systems so that symptoms of antenatal depression are identified early and women have easy access to empirically supported treatments. The objectives of this study are to evaluate symptoms of antenatal depression among adult pregnant women in Finland using population-based screening, evaluate the efficacy of the Stronger Together iCBT intervention for treating symptoms of antenatal depression, and examine possible treatment moderators. The primary hypothesis is that the iCBT intervention will reduce self-reported symptoms of antenatal depression, measured by the Edinburgh Postnatal Depression Scale (EPDS), compared to the educational information (allocation ratio 1:1). The secondary hypothesis is that the iCBT intervention group will report fewer symptoms of generalized anxiety, pregnancy-related anxiety, and personal stress after treatment than the educational control group. This hypothesis is based on the literature; psychosocial interventions for perinatal depression have been found to be effective also for anxiety and stress (12).

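### The Perceived Stress Scale is a secondary outcome, but the printed schedule collects it only at baseline, so the stress part of the secondary hypothesis could not be tested

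*Protocol article*

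**What the plan says.** The secondary hypothesis in the Introduction is that the intervention group "will report fewer symptoms of generalized anxiety, pregnancy-related anxiety, and personal stress after treatment than the educational control group". The Discussion part of the Abstract also lists stress among the symptoms the intervention is expected to reduce.

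Section 2.8 (Secondary outcomes) includes the PSS, which "examines changes in personal stress levels". It also defines the variable: "The total score, which we will evaluate, ranges from 0 to 40".

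Section 2.16 (Analysis plan) has the secondary outcomes modelled in the same way as the primary one. That means the follow-up score and the change from baseline, adjusted for the baseline score and study site.

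The schedule is Table 3 in section 2.7, whose footnote reads "T0 is baseline, T1 is immediately after the intervention, and T2 is 11 weeks after randomization". Its row "Perceived stress PSS" carries a mark at T0 and nowhere else. No other section gives a follow-up time for the PSS.

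**The concern.** A change score, or a baseline-adjusted comparison at follow-up, needs a value after randomization. Table 3 provides none for the PSS. If the follow-up questionnaires were built from that table, neither arm would have a PSS value at 11 weeks, and the stress part of the secondary hypothesis would have no data.

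The loss would be permanent for each woman who passes the 11-week visit. The PSS asks about the preceding month, so a missed value cannot be collected later. Imputation would have no observed follow-up PSS in either arm to draw on.

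There is also a reporting problem, even if the data exist. A reader of the published plan could not tell whether a later PSS result was prespecified, or whether its absence was selective.

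**Working it through.** The finding rests on comparing parts of the article; no sample-size input affects it.

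**1. What the text requires of the PSS**

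| Place | What it requires |
|---|---|
| Introduction, secondary hypothesis | Between-group comparison of stress after treatment |
| Abstract, Discussion | Reduction in stress |
| Section 2.8 | Change in stress; total score evaluated |
| Section 2.16 | Follow-up score and change, adjusted for baseline |

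All four need at least one PSS value after randomization.

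**2. What Table 3 schedules**

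| Row | T0 | T1 | T2 |
|---|---|---|---|
| EPDS | X | | X |
| BDI-II | X | | X |
| GAD-7 | X | | X |
| PRAQ-R2 | X | | X |
| SPIN | X | | X |
| MAAS | X | | X |
| PSS | X | | |
| Quality of life and sleep | X | | X |

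Seven of the eight self-report outcome rows have a follow-up mark. The PSS row is the exception.

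**3. Is the blank cell a text-extraction fault?** The PSS row was compared with the rows directly above (MAAS) and below ("Quality of life and sleep"). Each of the three has seven cells, counting the label. In the two neighbours the marks fall under T0 and T2. In the PSS row the only mark falls under T0, and the T2 cell is present and empty. A shifted column does not explain it.

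**4. Could T1 supply the value?** No. The PSS has no mark at T1, and the only measures marked there are the treatment-related ones, which section 2.12 restricts to the intervention group.

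**5. Size**

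- The plan's figures (section 2.15): 278 per group, and 278 × 1.14 = 316.92, which rounds up to the stated 317 per group.
- Planned enrolment: 2 × 317 = 634.
- Expected at follow-up with 14% attrition: 634 × (1 − 0.14) = 545.24, about 545.
- PSS follow-up values under Table 3: 0.
- Secondary scales affected: 1 of 5 (BDI-II, GAD-7, PRAQ-R2, SPIN, PSS).
- Components of the Introduction's secondary hypothesis affected: 1 of 3 (generalized anxiety, pregnancy-related anxiety, personal stress).

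**The case against.** The strongest reply is that one blank cell stands against four statements that presuppose a follow-up PSS, so an omitted mark is at least as plausible as an omitted assessment. Table 3 may also not be the full operational schedule. The booster sessions of section 2.4 do not appear in it, and section 2.11 places the buccal swabs in mid-pregnancy while the table marks them at T0 and T2. On this view the forms in use may be correct, and the most one can ask is that the sponsor check.

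Much of this stands. The article cannot show whether the fault lies in the table or in the data collection. The lost data are therefore conditional on Table 3 being followed. The count of 634 is planned enrolment, and the loss specific to the PSS is nearer 545, since the plan already expects to lose the rest. Nothing suggests that anyone deliberately chose to measure a change outcome once.

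It does not remove the contradiction. Nor can the gap be put down to condensation for a journal. The article prints the schedule, and section 2.7 names Table 3 as the place where the outcomes are set out: "The primary and secondary outcomes have been described in detail in" that table. A stated schedule conflicts with a stated outcome and hypothesis, and one of them has to change.

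**Conclusion.** The concern holds. As printed, the plan names a change outcome and a hypothesis about stress, and schedules no measurement from which either could be evaluated. If Table 3 is followed, the PSS is missing at follow-up for every woman: 634 enrolled, about 545 of them expected to reach follow-up. One of five secondary scales and one of three components of the secondary hypothesis then drop out.

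The mismatch between text and table is certain. Actual loss of data is not, because it depends on whether the T2 forms match the table, which the article does not show. The primary EPDS outcome, its sample size and its analysis are not touched.

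It still needs fixing promptly. Section 2.2 says recruitment is ongoing in all areas, and if the scale is missing from the forms, each further woman who completes follow-up adds an unrecoverable missing value.

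**What to change.** 1. Check first. Inspect the T2 online questionnaire and its paper version for the PSS, in both arms.
2. If the PSS is already collected at T2, correct Table 3 by adding the T2 mark. This costs one table cell.
3. If it is not, add the 10-item PSS to the T2 questionnaire for both arms now, and mark it in Table 3. Record the start date, analyze the women followed up after that date, and disclose the reduced sample when reporting. This costs ten questions per woman.
4. If the sponsor decides that the PSS is a baseline measure only, take it out of section 2.8 and take stress out of the secondary hypothesis and the Abstract. Do this by a dated and justified amendment.

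Whichever applies, document it before the treatment code is opened.

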### Additional outcomes

2.9

*Maternal attachment*. The total score of a shorter 12-item version of the Maternal Antenatal Attachment Scale (MAAS) (47) is used to evaluate antenatal attachment. This scale focuses on maternal attitudes, thoughts, feelings, and behaviors toward the growing fetus, and higher scores indicate a more adaptive mother–infant bonding style. This scale has an internal consistency of 0.73 (48) and has not been validated in Finland.

*Sleep and quality of life.* Single questions regarding quality of life, loneliness, satisfaction with social relationships, and sleep are administered. Each question is analyzed separately.

### Background measures

2.10

Sociodemographic and health-related data, including age, family structure, level of education, employment, and chronic diseases, are collected at baseline. This includes detailed information about previous psychiatric diagnoses and their treatment, smoking, substance abuse, and previous pregnancies and childbirth. Further, the women are asked about meaningful life events 12 months before the beginning of the study.

### Biological samples

2.11

Biological samples are collected to explore possible biological mediators for therapeutic response. Maternal serum samples are collected from all mothers who give permission to use their previously collected samples at antenatal clinics for study purposes in the screening phase. Buccal cell swabs are collected from the women in mid-pregnancy. The polygenetic risk scores for depression will be calculated, and the association between the genetic risk scores and the treatment responsiveness will be explored. The inflammatory markers and epigenetic alterations will be determined by examining the differences in DNA methylomes based on the treatment responsiveness.

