**Methods:**

This ongoing research project evaluates the efficacy of the *Stronger Together* internet-assisted cognitive behavioral therapy (iCBT) with telephone coaching for antenatal depression. It is a large, population-based, two-parallel group, randomized controlled trial. The overarching hypothesis is that iCBT programs are easy to access and affordable and will reduce self-reported symptoms of antenatal depression better than an educational control. The intervention group is also expected to report fewer anxiety symptoms after treatment than the control group. The protocol follows the Standard Protocol Items: Recommendations for Interventional Trials (SPIRIT) guidelines. The study population consists of all Finnish- or Swedish-speaking women, aged ≥18 years, who attend maternity health check-ups at 13–18 weeks of gestation in selected areas of Finland. The aim is to recruit all women who exceed 10 points on the Edinburgh Postnatal Depression Scale and meet other eligibility criteria. Other measures used are the Beck Depression Inventory-II, the Generalized Anxiety Disorder 7-Item Scale, the Pregnancy-Related Anxiety Questionnaire-Revised, the Social Phobia Inventory, and the Perceived Stress Scale. In addition, biological samples (maternal sera and buccal cells) are collected to explore possible moderators for the treatment response. The primary data are collected at baseline and 11 weeks after randomization. The women are randomized 1:1 to the *Stronger Together* iCBT intervention, which combines seven-weekly themes on a digital platform with weekly telephone coaching, or the educational control group. The CBT components include psychoeducation, behavioral activation, coping with social relationships, cognitive restructuring, and preventing setbacks. The educational control group receives psychoeducational material about wellbeing during pregnancy. Both groups continue to receive standard treatment and maternity health check-ups.

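### Section 2.11 calls the biological samples mediators where the abstract says moderators, and relating them to undefined treatment responsiveness, read as observed response, cannot separate effect modification from prognosis

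*Protocol article*

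**What the plan says.** The Methods paragraph of the abstract states that "biological samples (maternal sera and buccal cells) are collected to explore possible moderators for the treatment response". The Introduction names, as one of the study objectives, to "examine possible treatment moderators".

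Section 2.11 gives the same samples another role: "Biological samples are collected to explore possible biological mediators for therapeutic response". It then states two analyses. For the polygenic scores, "the association between the genetic risk scores and the treatment responsiveness will be explored". Inflammatory markers and epigenetic alterations are to be studied by "examining the differences in DNA methylomes based on the treatment responsiveness". Treatment responsiveness is not defined, and neither an arm nor a contrast between arms is named.

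On timing, serum comes from women who give "permission to use their previously collected samples at antenatal clinics for study purposes in the screening phase", and Table 3 marks it at T0 only. For buccal cells, section 2.11 says "Buccal cell swabs are collected from the women in mid-pregnancy", while Table 3 marks swabs at both T0 and T2.

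The model in section 2.16 has baseline EPDS and study site as covariates and no marker term.

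**The concern.** Moderator and mediator are different causal roles. A moderator is a pre-treatment characteristic across which the effect of iCBT against control varies. A mediator is changed by iCBT and carries part of its effect. The two need different data and different analyses, so the document should not use both words for one set of samples.

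The stated analysis adds to the difficulty. Individual response to treatment is not observed in a parallel-group trial. A woman's observed change mixes the treatment effect, the natural course and regression to the mean. The last matters here because women enter by reaching EPDS cutoffs (at least 10 at screening and at least 9 at baseline, Table 1). A marker associated with observed change may therefore predict course equally well in both arms and say nothing about who benefits from iCBT. At stake is that a prognostic marker is reported as one of therapeutic response, or that a real moderator is overlooked.

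**Working it through.** **Which markers can have which role**

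| Marker | Timing in the document | Can moderate | Can mediate |
|---|---|---|---|
| Polygenic score | Fixed genetically | Yes | No |
| Serum markers | Previously collected sample; T0 only (Table 3) | Yes | No |
| Buccal methylation at T0 | Before treatment | Yes | No |
| Buccal methylation change, T0 to T2 | After randomization (Table 3) | No | Possible |

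The word in section 2.11 can fit only the last row.

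**Background figures (section 2.15).** With a difference of 1.5, SD 6.30, two-sided α = 0.05 and 80% power, the two-sample t-test needs 277.87, so 278 per group. This matches the document. Enrolling 317 per group with 14% attrition leaves 317 × 0.86 = 272.6, about 273 evaluable per group. The document gives no figure for the biomarker analyses, so the marker slopes below are assumptions.

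**Purely prognostic marker, observed response in the iCBT arm.** The marker is standardized, has the same slope in both arms and has no moderating effect.

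- SE of the slope = 6.30/√273 = 0.381.
- Slope 0.5: z = 0.5/0.381 = 1.31; rejection ≈ Φ(1.31 − 1.96) ≈ 26%.
- Slope 1.0: z = 1.0/0.381 = 2.62; rejection ≈ Φ(2.62 − 1.96) ≈ 75%.
- Arm-by-marker interaction: the true value is zero, so rejection is 5%.

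**Simulation check.** 3,000 replicates, 278 women per arm, SD 6.30, main effect −1.5. Entries are the share of trials with p < 0.05.

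| Slope in control / iCBT | iCBT arm only | Both arms pooled, adjusted for arm | Interaction |
|---|---|---|---|
| 0 / 0 (null) | 4% | 5% | 5% |
| 1.0 / 1.0 (prognostic only) | 77% | 97% | 4.5% |
| 1.5 / 1.5 (prognostic only) | 98% | 100% | 5% |
| −0.75 / +0.75 (true moderator) | 51% | 5% | 80% |
| −1.5 / 0 (true moderator) | 4% | 82% | 83% |

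The iCBT-only association misses the moderator in the last row, and the pooled association misses the one in the row above it. Where the pooled association does flag a moderator (82%), it flags a prognostic marker as readily, so it does not identify which is which.

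**Limit of the illustration.** The slope must be on change or on baseline-adjusted follow-up. Suppose instead that a marker shifts baseline and follow-up EPDS by the same amount b. Its association with change is b − b = 0. In a model of follow-up adjusted for baseline, with β the coefficient of baseline, its slope is b − βb = b(1 − β), smaller than b when β lies between 0 and 1. Such a marker is flagged less often, or not beyond the 5% error rate.

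**What the interaction test can detect.** With 278 × 2 = 556 women, SE = 6.30 × √(4/556) = 0.534 per SD of marker. Detectable with 80% power: (1.96 + 0.84) × 0.534 ≈ 1.5 EPDS points per SD. For a marker split 50/50, the SE doubles to 1.07 and the detectable difference in effect is about 3.0 points, twice the planned main effect. Both figures assume marker data for all 556 women.

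**The case against.** The strongest reply is that this is a condensed article. How an exploratory biomarker association is modelled is commonly left to an analysis plan or sub-study plan, and responsiveness to treatment could be read as a treatment effect that varies with the marker, which would agree with the abstract. This stands in part: the article does not rule out an interaction test, and the mere lack of a model specification is no fault. It does not remove the conflict between moderators and mediators. Nor does it fully answer the methylome sentence, which as written compares women by their responsiveness and names no contrast with the randomized control.

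Second, nothing in section 2.11 confines the analysis to the iCBT arm. Section 2.12 does limit its own measures to that arm, so the silence in 2.11 may be deliberate. This stands, and the 26% to 75% is therefore one reading. The pooled reading does not rescue the analysis, as the simulation shows.

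Third, the percentages rest on assumed slopes and on complete marker data, although serum depends on permission. This also stands; they illustrate the problem and do not predict a rate.

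Fourth, the document already describes the work as exploratory, and mediation is possible for buccal methylation. Both are correct. The text plans no confirmatory biomarker claim, and the word needs narrowing, not removal.

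**Conclusion.** The contradiction is established from the text alone: the abstract says moderators, section 2.11 says mediators, and most of the listed markers cannot mediate because they are fixed before treatment. The weakness of the stated analysis holds if treatment responsiveness means observed response, whether in one arm or pooled. Under the assumptions shown (slope of 0.5 to 1.0 point per SD on baseline-adjusted EPDS, SD 6.30, about 273 iCBT women with marker data), a marker with no moderating effect would be flagged in about 26% to 75% of trials instead of 5%.

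A reader might infer that the trial's moderator objective as a whole would be answered wrongly. The document does not support that. The objective in the Introduction is not limited to biomarkers, section 2.10 lists baseline characteristics that could also serve as moderators, and nothing says section 2.11 is the entire moderator analysis. Nor does the point touch the primary or secondary efficacy conclusions or the sample size. It is a correction worth making to an exploratory part of the trial.

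**What to change.** In section 2.11:

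- Use moderators for the polygenic score, the serum markers and the T0 buccal markers.
- Replace the association with responsiveness by an arm-by-marker interaction in the EPDS model adjusted for baseline EPDS and site, using women with marker data in both arms.
- Keep mediators only for buccal methylation change from T0 to T2, compared between arms, and bring the swab timing in the text into line with Table 3.
- Keep the existing exploratory status.

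The cost is wording and analysis code. Both arms, the EPDS at T0 and T2, and the samples are already planned. Recruitment was still ongoing when the article was written (section 2.2), so the change can be made before the treatment code is opened. The downside is power: only interactions of about 1.5 EPDS points per SD or more would be found with 80% power, even with marker data for all 556 women, so fewer markers will be declared.
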